# Effects of transcranial direct current stimulation on the rehabilitation of painful shoulder following a stroke: protocol for a randomized, controlled, double-blind, clinical trial

**DOI:** 10.1186/s13063-019-3266-y

**Published:** 2019-03-15

**Keywords:** Stroke, tDCS, Shoulder pain, Rehabilitation

## Abstract

**Background:**

Shoulder pain is reported to be one of the major challenges faced in the functional recovery of patients in rehabilitation following a stroke. In such cases, transcranial direct current stimulation (tDCS) has been used as an additional therapeutic tool for improvements in central and peripheral pain. The aim of the proposed study is to evaluate the effect of tDCS when combined with upper limb physical therapy on pain intensity and functional improvement in stroke survivors with shoulder pain in the hemiplegic limb.

**Methods:**

A randomized, placebo-controlled, double-blind, clinical trial is proposed. The volunteers will be randomly allocated to receive passive movement on the upper limb, which will be performed by the therapist for 20 min followed by either active tDCS or sham tDCS (current stimulation for 30 s) during simultaneous physical activity of the upper limb (“mini-bike”) for 20 min, totaling 40 min of intervention performed in 10 consecutive sessions. The anode electrode will be positioned over the primary motor cortex with a current of 2 mA and the cathode electrode will be positioned in the supraorbital region contralateral to the anode. The primary outcome will be shoulder pain intensity, which will be measured using the visual analog scale (VAS) on three occasions: 1) pre-intervention; 2) after 10 interventions (5 weekly sessions, for 2 weeks); and 3) 30 days after the end of the interventions. The secondary outcomes will be motor performance, upper limb function, and quality of life.

**Trial registration:**

Brazilian Registry of Clinical Trials, RBR-8F5MNY. Registered on June 2, 2017.

**Electronic supplementary material:**

The online version of this article (10.1186/s13063-019-3266-y) contains supplementary material, which is available to authorized users.

## Background

Stroke is the second most common cause of death and the third most common cause of disability [1]. This condition is therefore considered an important public health problem throughout the world due to the social and economic impacts stemming from motor, cognitive, and/or sensory impairments, which have a negative impact on the performance of activities of daily living [2].

Shoulder pain is a frequent complication of a stroke, with an incidence ranging from 34% to 85% [3]. It may start in the second week after a stroke, but its onset is much more frequent 2 to 4 months after the event [4]. Although some cases of poststroke shoulder pain disappear spontaneously throughout the rehabilitation process, 65% of stroke survivors report the persistence of this symptom, which may extend for 12 months or longer. According to the International Association for the Study of Pain (IASP) [5], 3 consecutive months with pain sensation may be considered the cut-off point for the division between acute and chronic pain, but 6 months is often used for purposes of research.

The pathophysiology of shoulder pain poststroke may have multifactorial causes. Authors suggest that it may be related to spasticity [6], musculoskeletal alteration [7], limitation of shoulder movements and subluxation, rotator cuff damage and changes in the general glenohumeral joint [8, 9], psychological factors and central changes [10, 11] due to thalamic and spinothalamic tract damage [12, 13].

The assessment and treatment of poststroke shoulder pain (PSSP) is largely based on the assumption that pain is due to biomechanical alterations within the shoulder joint after stroke. However, current treatment often provides limited pain relief, leading to a considerable number of patients with persistent pain. This suggests that PSSP may not be merely due to simple nociception from the shoulder joint [14]. Sensitization and possibly disinhibition seem to play a role in the chronic maintenance of this pain in the shoulder after stroke, and may explain why treatment aimed at reducing peripheral nociception is generally unsatisfactory. Unlike acute pain, chronic pain is no longer functional and may no longer be related to the initial cause. The underlying mechanisms for the development of chronic pain are not well understood. It is suggested that chronic pain is due to an imbalance of somatosensory inhibitory and excitatory modulation, favoring the facilitation of nociception [15].

The supraspinal somatosensory system may become sensitized, uninhibited, and/or functionally [16] or structurally reorganized [17] as a result of ongoing nociception. A reorganization of the primary sensory and motor cortex is reported to occur in a variety of chronic pain conditions [18–20]. Findings of cortical disinhibition in different chronic pain conditions provide further evidence of the interrelationship between motor and nociceptive systems and suggest a potential mechanism to explain the efficacy of stimulation of the primary motor cortex (M1) as a treatment modality for chronic pain. M1 is the main site selected for transcranial direct current stimulation (tDCS), which has significant analgesic effects in chronic pain conditions [21].

tDCS is defined as a noninvasive brain stimulation technique with neuromodulatory action that alters cortical activity and excitability [22, 23]. It is characterized by a continuous current of low intensity sufficient to decrease the depolarization threshold and, therefore, to facilitate the action potential in the neurons, as seen by researchers [24] that observing the effects of the anodic and cathodic tDCS when applied on the motor cortex with intensities of 0.2 and 1.0 mA for between 1 and 5 min. Among the observed effects, cortical excitability and amplitude of the motor evoked potential were increased by approximately 40% by the anodic tDCS, as well as a 30% reduction in motor evoked potential amplitude after cathodal stimulation. Thus, it is believed that the technique is able to modulate cortical excitability by altering the cellular potential of the membrane.

One study with fibromyalgia syndrome reports that increased excitability of this region of the brain enables the enhancement of motor control and, consequently, better pain control [25]. Another study reports that long periods of cortical stimulation can have lasting effects on brain function, with an increase in the intrinsic plasticity of the motor sensory system and the enhancement of the effects of other therapeutic tools [26]. In a study investigating the effect of tDCS administered over M1 on pain in patients with spinal cord injury, better effects were found when compared with sham tDCS [27]. In an investigation of the analgesic effects in different parts of the body of tDCS with anodal stimulation over M1 in patients with central poststroke pain, the authors found an improvement in sensory identification and analgesic effects [28]. No tDCS studies have been found in shoulder pain due to stroke.

There is evidence that pain relief in patients with chronic pain submitted to noninvasive brain stimulation may be related to the restoration of normal corticospinal and intracortical excitation induced by such stimulation [29, 30], as demonstrated in studies involving tDCS [31, 32]. According to some researchers, the effect of tDCS on chronic pain is due to the reinforcement of intracortical inhibition and a reduction in overfacilitation [33, 34].

The modulation of intracortical inhibition is also critical for fine motor control (the selective activation of muscles during motor tasks) [35] and is an important aspect of neuroplasticity associated with motor learning and rehabilitation [34, 36]. For example, experimental models involving conditioning tasks that result in a reduction in the stimulation of subliminal conditioning have been shown to impair subsequent motor learning tasks [37, 38], demonstrating the limitation of plasticity in the motor cortex [39]. Thus, it is possible that ongoing cortical disinhibition may be associated with impaired motor performance and motor learning in individuals with chronic pain.

Considering the relationship between pain and motor performance and the fact that long periods of cortical stimulation can have lasting effects on brain function, such as an increase in the intrinsic plasticity of the motor sensory system and the enhancement of the effectiveness of other therapeutic tools, it is believed that the combination of tDCS and physical therapy may lead to a reduction in pain. This combined therapy is expected to enhance the motor performance of patients with PSSP as well as improve both sleep quality and quality of life. Indeed, stimulation is effective at relieving a number of chronic pain conditions, especially in patients who are resistant to drug therapy [26, 40].

Therefore, the aim of the proposed study is to evaluate the effect of tDCS, when combined with upper limb physical therapy, on pain level and functional improvements in stroke patients with hemiplegic shoulder pain. As a secondary endpoint, we intend to correlate the analgesic effects of tDCS therapy and upper limb physical activity with the effects on motor performance and determine the influence of this therapeutic modality on sleep quality and quality of life.

## Methods

### Study design

A randomized, placebo-controlled, double-blind, longitudinal, clinical trial is proposed.

The primary outcome of this study will be the intensity of shoulder pain, which will be measured using the visual analog scale (VAS). The VAS will be administered on three occasions): 1) pre-intervention; 2), after 10 interventions; and 3) 30 days after the end of the interventions. The secondary outcomes are motor performance and quality of life.

Participants will be recruited from the physical therapy clinics of the University Nove de Julho, São Paulo, Brazil.

The SPIRIT checklist can be found as Additional file 1. The evolution of the study is shown in Fig. 1.

**Fig. 1 Fig1:**
[figure not shown]
Diagram of the study. tDCS transcranial direct current stimulation

### Eligibility criteria

Individuals who meet the following inclusion criteria will be asked to participate in the study: 1) adults (> 18 years of age) with a diagnosis of chronic stroke [41] (there are few studies proving the safe administration of tDCS in the acute and subacute phases of a stroke, hence the choice of chronic stroke) and complaint of shoulder pain after stroke for at least 6 months (the ideal time for research on chronic pain, according to the IASP) [5]; and 2) able to understand commands (Mini-Mental State Examination score > 11) [42].

The exclusion criteria are: 1) contraindication for noninvasive brain stimulation (metal implants near application sites, history of seizures and/or epilepsy, pregnancy, and diagnosis of neoplasm); 2) muscular inelasticity (spasticity) > 3 on the affected upper limb, evaluated by the Modified Ashworth Scale [43]; 3) progressive neurological disease; 4) diagnosis of frozen shoulder; 5) severe sensory deficit (score > 2 on the National Institutes of Health (NIH) Stroke Scale) [44]; 6) diagnosis of acute coronary syndrome or severe heart problems (score > 3 on the New York Heart Association functional classification scale) [45]; 7) severe aphasia (score > 2 (evaluated in patient’s native tongue) indicated by NIH Stroke Scale) [44]; 8) suspicion or confirmation of recent upper limb fracture; 9) diagnosis of cancer and/or in therapy for palliative care; and 7) severe inattention (score > 2 indicated by NIH Stroke Scale) [44]. Concomitant care and interventions prohibited during the trial will be the recent use of botulinum toxin or phenol injection in the affected upper limb (in the previous 3 months) or a medical indication for use during the study period, the use of medications that can affect the evaluations (steroidal anti-inflammatory drugs), and participation in physical or homeopathic therapy during the study.

### Sample size

For the calculation of the sample size, the primary endpoint of the study (shoulder pain intensity at rest measured by VAS) was considered to be directly related to the intervention and has been widely used for this purpose. The calculation was performed considering a level of significance (alpha) of 0.05 and an 80% study power, considering a clinically important difference of ≥ 3 points on the VAS [46]. Based on the results of a pilot study involving 10 individuals with PSSP (five for the active group and five for the sham), the difference between the means was 3.0 in the group submitted to physical therapy, and active tDCS and 1.56 in the submitted group to physical therapy and sham ETCC, with a combined standard deviation of 1.38, the required sample size was 22 subjects (11 per group). Taking into account the possibility of dropouts, the sample was increased by 20% to ensure a sample size that enables us to demonstrate the effect of the intervention, leading to 13 individuals in each group (total of 26 participants). This calculation was performed using the G*Power software.

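### The sample size is presented as resting on a clinically important difference of at least 3 VAS points, but its pilot inputs imply a between-arm difference of 1.44, and 3 points cannot have produced 22 subjects.

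*Protocol article*

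**What the plan says.** All the figures are in one paragraph, the Sample size section of the protocol article. The primary endpoint is shoulder pain at rest on the VAS. The section introduces the calculation with the words "considering a level of significance (alpha) of 0.05 and an 80% study power, considering a clinically important difference of"; the value it then gives for that difference is 3 VAS points or more.

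The next sentence gives the pilot results (five patients per arm). For the active arm it reports that "the difference between the means was 3.0 in the group submitted to physical therapy, and active tDCS". The matching figure for the sham arm is 1.56, and the SD for both arms together is 1.38. From these it reports 22 subjects, 11 per group, raised to 13 per group for dropout. G*Power is named as the software. The test, the sidedness and any correlation between assessments are not given.

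The Data analysis section plans ANOVA with Bonferroni, or non-parametric tests if normality is rejected, and takes p < 0.05 as the mark of statistical significance.

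**The concern.** The trial compares active with sham stimulation, both added to the same physical therapy. The difference to be powered is therefore the one between the arms. In the pilot inputs only the active arm's own figure reaches 3, and the sham arm reached 1.56 without active stimulation. The between-arm difference is less than half of the figure that the paragraph offers as its target.

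The stated target and the sized target are thus different quantities, and the paragraph does not say so. A reader would take the trial to have been sized at 80% power for a 3-point benefit of tDCS. If 3 points is meant as a between-arm threshold, a significant result could correspond to an effect well below it.

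**Working it through.** **Inputs (Sample size section).** Alpha 0.05, sidedness not stated; power 80%; stated difference at least 3; pilot figures 3.0 and 1.56; SD 1.38; 11 per group. The three VAS assessments are in the Study design section. The SD is taken to apply to the quantity compared between arms, which the article does not say.

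**Implied difference.** 3.0 − 1.56 = 1.44, and 1.44/3 = 48%. Standardised: 1.44/1.38 = 1.043, against 3/1.38 = 2.174.

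**Can the stated 22 be reproduced from 1.44?**

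- *Repeated-measures ANOVA, between-groups effect.* Effect size f = d/2 = 1.043/2 = 0.522. Noncentrality λ = f²·N·m/(1 + (m − 1)ρ), with m = 3 assessments and an assumed correlation ρ = 0.5. For N = 22, λ = 0.272 × 22 × 3/2 = 8.98, and the critical F(1, 20) is 4.35, so power is 0.813. For N = 20 power is 0.771. The smallest even N is therefore 22, as stated. For correlations from 0.3 to 0.8 the required N runs from 18 to 28.
- *Two-sided two-sample t test.* Noncentrality = d·√(n/2). For n = 11 this is 1.043 × √5.5 = 2.45, and power is 0.64. At 15 per arm power is 0.79 and at 16 it is 0.81, so 16 per arm (32 in total) are needed.
- *One-sided t test.* 13 per arm (26 in total).

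**Can 22 be reproduced from 3 points?**

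- *Two-sided t test.* At n = 4 power is 0.73. At n = 5 the noncentrality is 2.174 × √2.5 = 3.44 and power is 0.85. So 5 per arm, 10 in total.
- *Repeated-measures ANOVA, three assessments.* 8 to 10 in total for correlations from 0.3 to 0.8.
- *Power at 11 per arm, two-sided t test.* Noncentrality 2.174 × √5.5 = 5.10, power 0.998, against the stated 80%.
- *Larger SD.* With 1.38 × √2 = 1.95 the t test needs 8 per arm, still not 11. For 3 points to require 11 per arm at 80% power, the SD would have to be about 2.39.

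**What an observed 1.44 would show.** The half-width of a two-sample t interval is t(0.975, 2n − 2) × 1.38 × √(2/n).

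| n per arm | half-width | 95% CI around 1.44 |
|---|---|---|
| 13 | 2.064 × 1.38 × 0.392 = 1.12 | 0.32 to 2.56 |
| 11 | 2.086 × 1.38 × 0.426 = 1.23 | 0.21 to 2.67 |

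Both intervals exclude 3. At 13 per arm an observed difference of about 1.12 points would already be significant.

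**The case against.** **The article never prints 1.44.** This stands. That 1.44 was the input is an inference. It matches 22 only under an assumed method and correlation, and the ordinary two-sided t test on 1.44 does not give 11 per group. Another route also reaches 11 per group: a one-sided t test on 1.56 with SD 1.38 (power 0.82), although 1.56 is the sham arm's own figure and not a contrast between the arms. What does not depend on the inference is that 3 points with SD 1.38 gives nothing near 22.

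**The 3 points may be a within-patient threshold.** The active arm's pilot figure is exactly 3.0, so the sentence may mean that treated patients were expected to reach an important change. The article does not say, and neither reading can be assumed. On this reading 3 points still did not set the sample size, although the paragraph presents it as the difference considered. A between-arm interval that excludes 3 would then say nothing about clinical importance.

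**Power for 3 points is not lost.** Correct. Sizing on a smaller difference gives more power for 3 points, so a reader should not infer that the trial is too small for its stated target.

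**The protocol does not equate significance with benefit.** Also correct. A reader might infer that a trial going as planned would rule out a clinically important effect. The documents support this only if 3 is a between-arm threshold, and only under a t interval with an SD taken from five patients per arm. The planned analysis may give a different interval.

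**Conclusion.** The paragraph is wrong as written. It ties 80% power to a difference of at least 3 points, while its inputs imply a between-arm difference of 1.44. A 3-point between-arm target with SD 1.38 leads to 8 to 10 patients in total, not 22. This is a conflict between figures printed side by side, not a detail that an article leaves to a fuller document.

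The conclusion rests on SD 1.38 being the SD for the arm comparison. That 1.44 was the value entered is probable, not proven. Whether 3 points is a within-patient or a between-arm threshold is open. The interval of 0.32 to 2.56 matters only in the second case and is conditional on the pilot SD and a t analysis. The comparison between arms remains valid; what is misstated is the effect for which the trial was sized.

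**What to change.** Reword the Sample size section so that it:

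1. states that the trial is sized for a between-arm difference of 1.44 VAS points, with the test, sidedness and, if a repeated-measures model was used, the correlation and number of assessments entered in G*Power;
2. states that the figure of at least 3 points is not the powered between-arm difference, and whether it is a within-patient or a between-arm threshold;
3. if it is a between-arm threshold, adds that a significant result would not by itself show a clinically important effect, with the conditional interval (observed 1.44, 13 per arm, SD 1.38: 0.32 to 2.56) as illustration.

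No extra patients, visits or measurements follow from this rewording. The cost is a few sentences and a less favourable stated target. If the calculation turns out to have been a two-sided t test on 1.44, the text should not claim 80% power at 11 per arm, because that design has 64%.

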#### Data analysis

Descriptive data and characteristics of the patients (gender, age, initial score on the VAS, ischemic or hemorrhagic stroke, right/left hemisphere lesion, time with pain, injury time, Fugl-Meyer upper limb score, BDI, use of controlled medications, and associated comorbidities) will be represented by mean and standard deviation or median and interquartile range. The normality of the data from the VAS, DASH, Fugl-Meyer, SSQOL, range of motion passive shoulder, and hand grip strength will be analyzed by the Shapiro-Wilk test.

If the normality hypothesis is accepted, the analysis of variance (ANOVA) followed by the Bonferroni test will be used, when necessary, to perform the comparison analysis between groups. If the normality hypothesis is rejected, the Kruskal-Wallis test will be used. The Mann-Whitney test will be used to compare the results of the study treatment periods (pre- and post-treatment and 30-day follow-up). Pearson or Spearman correlation coefficients will be calculated to determine the strength of correlations between pain and secondary outcomes (SPADI, Fugl-Meyer, SSQOL, passive shoulder range of motion and grip strength). A value of *p* < 0.05 will be considered indicative of statistical significance. All analyses will be processed using the SPSS program (IBM SPSS Statistics for Windows, Version 22.0, released in 2013, IBM Corp., Armonk, NY, USA).

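### The stated 80% power with 11 per group is not supported for the between-group question: a two-sided comparison on the pilot figures has about 64%, and the route that gives 22 counts a treatment difference at baseline

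*Protocol article*

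**What the plan says.** All of the following is in the Sample size section of the protocol article unless noted.

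- Error rates: "level of significance (alpha) of 0.05 and an 80% study power". Sidedness is not given. The Data analysis section says only that p < 0.05 "will be considered indicative of statistical significance".
- First target: "considering a clinically important difference of ≥ 3 points on the VAS".
- Pilot result (five patients per group): "the difference between the means was 3.0 in the group submitted to physical therapy, and active tDCS and 1.56 in the submitted group" given sham stimulation.
- Spread and result: "with a combined standard deviation of 1.38, the required sample size was 22 subjects (11 per group").
- Dropout: "Taking into account the possibility of dropouts, the sample was increased by 20"%, "leading to 13 individuals in each group (total of 26 participants").
- Tool: "This calculation was performed using the G*Power software". The test chosen within it is not named.

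Pain is measured before treatment, after the ten sessions and 30 days later. The Data analysis section plans ANOVA for the comparison between groups, or Kruskal-Wallis if normality is rejected. It does not say whether the ANOVA is a repeated-measures one, and it describes no baseline adjustment of the VAS.

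**The concern.** The section publishes its inputs and its result, so a reader can try to connect them. The simplest connection, two groups compared two-sidedly on the 1.44-point difference, does not lead to 11 per group. If the trial has materially less than 80% power for the effect it was sized on, a real effect of pilot size could be missed in more than one trial in three. A null result would then be read as coming from an adequately powered trial. The section also gives two targets, 3 points and 1.44 points, that imply very different sample sizes.

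**Working it through.** **Inputs.** From the Sample size section: mean differences 3.0 and 1.56, SD 1.38, alpha 0.05, target power 80%, equal groups of 11 (13 after inflation). I read 3.0 and 1.56 as within-group improvements, so the between-group difference is 3.0 − 1.56 = 1.44 and d = 1.44/1.38 = 1.043.

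**Step 1: reproducing 22.** For the between-groups main effect of a repeated-measures ANOVA, f = d/2 = 0.522 and the noncentrality is λ = f²·N·m / (1 + (m − 1)ρ), with 1 and N − 2 degrees of freedom. Take m = 3 visits and ρ = 0.5 (my assumption; the article gives no correlation).

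- N = 20: λ = 8.17, power 77.1%.
- N = 22: λ = 0.522² × 22 × 3 / 2 = 8.98, power 81.3%.

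The smallest even N reaching 80% is 22, which matches the article.

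**Step 2: what that route assumes.** It takes a 1.44-point difference at all three visits, including the one before treatment. If the baseline difference is zero and 1.44 is present at the two later visits, the average difference is 1.44 × 2/3 = 0.96. At N = 22 and ρ = 0.5, λ = 8.98 × 4/9 = 3.99 and power is 48%. With SD 1.38 at each visit, the range over ρ is:

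| Assumed ρ | Power, N = 22, effect only after baseline |
|---|---|
| 0.3 | 57% |
| 0.5 | 48% |
| 0.7 | 41% |

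**Step 3: two-group comparison of the 1.44-point difference.** Noncentral t with 2n − 2 degrees of freedom and noncentrality d√(n/2); at n = 11 this is 1.043 × √5.5 = 2.447.

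| n per group | Two-sided power | One-sided power |
|---|---|---|
| 10 | 59.8% | 72.6% |
| 11 | 64.4% | 76.4% |
| 13 | 72.3% | 82.6% |
| 16 | 81.5% | 89.2% |

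Two-sided, 15 per group gives 78.8%, so 80% needs 16 per group (32 evaluable). Rounding of the inputs moves the 64.4% only between 63.8% and 65.0%. The normal approximation gives 68.7% at 11 per group and needs 15 per group, which does not reach 11 either. The difference detectable with 80% two-sided power is 1.73 points at 11 per group and 1.58 points at 13.

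**Step 4: the 3-point target.** d = 3/1.38 = 2.17. Five per group gives 85% two-sided power, and 11 per group gives more than 99%. The figure 22 therefore does not come from the 3-point criterion.

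**Step 5: dropout.** 22 × 1.2 = 26.4, reported as 26. If 20% is the expected loss, 26 × 0.8 = 20.8 remain, about one patient short of 22.

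**The case against.** The strongest reply is that the article states no test, so no single power can be read from it. A reader might infer from the t-test figures that the 80% is a plain arithmetic error and that the trial's true power is 64%. The documents do not support that. The 64% requires a two-sided, single-contrast, unadjusted test that the article does not specify, and 22 does come out of a recognised calculation on the same difference and SD.

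Other readings would raise the power:

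- **One-sided alpha.** The normal approximation gives 78.9% power at 11 per group and asks for 12 per group. The one-sided t-test gives 76.4% and asks for 13. No one-sided test is mentioned anywhere, and the planned ANOVA and Kruskal-Wallis tests are non-directional.
- **Baseline adjustment.** If 1.38 is the SD of raw scores, an adjusted analysis at 11 per group has 68%, 77%, 83% or 90% power for an assumed baseline correlation of 0.3, 0.5, 0.6 or 0.7. The article does not say which SD 1.38 is and describes no such adjustment for the VAS.
- **Averaging only the two post-treatment visits.** With 1.44 at both, power at N = 22 is 82%, 77% or 71% for an assumed correlation of 0.3, 0.5 or 0.7. The article does not describe this analysis either.

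The reply on dropout also stands in part. The article says that the sample was increased by 20%, not that 20% are expected to leave, and the possible shortfall is about one patient.

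What remains is that the 80% rests on assumptions the article does not state. The one route found that returns 22 from the trial's three visits does not measure a difference in improvement.

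**Conclusion.** The concern holds in this form: the stated 80% power with 22 patients is not supported for the between-group question. For an unadjusted two-sided comparison, with 1.38 as the SD of the quantity compared, power is about 64% with 22 evaluable and 72% with 26. Reaching 80% takes 32 evaluable. The three-visit main effect that reproduces 22 has about 48% power once the baseline difference is set to zero (57% to 41% over assumed correlations of 0.3 to 0.7, with an equal effect at both later visits).

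These are conditional figures, and none of them should be presented as the trial's one true power. A baseline-adjusted analysis could reach 80% under favourable assumptions, but the article does not commit to one. The conflict between the 3-point and 1.44-point targets needs no assumption about the test. The dropout point is minor.

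**What to change.** Rewrite the sample-size paragraph as follows.

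1. Name the test, its sidedness, whether 1.38 is the SD of change or of scores, and any correlation between visits that was used.
2. State that the calculation targets the 1.44-point between-group difference, and reconcile this with the criterion of at least 3 points, for example by saying whether the latter refers to change within a patient.
3. Replace the 80% with the power of the analysis actually planned. If that is an unadjusted two-sided comparison, with 1.38 as the SD of the compared quantity, give about 64% with 22 evaluable and 72% with 26. Give 1.73 and 1.58 points respectively as the differences detectable with 80% power. If a baseline-adjusted analysis is adopted, recompute, because these figures will not apply to it.
4. Say whether 20% is the expected loss. If so, note that 26 enrolled leaves about 21 evaluable.

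The cost is one paragraph and, probably, a less favourable stated power. No additional patients are required.

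### The 20% increase for dropouts is rounded down to 13 per group, which keeps the plan's own 11 per group only up to about 15% loss

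*Protocol article*

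**What the plan says.** Everything relevant is in the Sample size section of the protocol article. The targets are a "level of significance (alpha) of 0.05 and an 80% study power". The pilot results are given as "the difference between the means was 3.0 in the group submitted to physical therapy, and active tDCS and 1.56 in the submitted group" (active and sham respectively), "with a combined standard deviation of 1.38". From these the section concludes that "the required sample size was 22 subjects (11 per group").

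The dropout step follows. The section says that "the sample was increased by 20% to ensure a sample size that enables us to demonstrate the effect of the intervention". The enrolment that results from this step is 13 per group, or 26 patients in all.

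The section does not say what proportion of patients is expected to drop out, and no other section of the article does. It names G*Power as the software, but neither the test nor whether it is one- or two-sided.

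**The concern.** An allowance for dropouts has one job: after the expected losses, the number left should still meet the requirement. Two things in this step work against that.

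- The increased figure is not a whole number and was rounded down. A sample size meant to secure a minimum is rounded up.
- Adding a percentage to the required number is not the same as allowing for that percentage of dropout. Adding 20% to a number and then losing 20% of the result leaves 96% of the starting number.

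At stake is whether the trial ends with its own stated minimum of 11 per group, to which the 80% power is tied. With so few patients there is little slack: a third loss in either arm takes that arm below 11. Patients must also be retained to the assessment 30 days after the last session (Data collection, management, and analysis).

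**Working it through.** **Inputs, all from the Sample size section.** Required: 11 per group, 22 in total. Increase: 20%. Enrolled: 13 per group, 26 in total. Pilot difference: 3.0 - 1.56 = 1.44. SD: 1.38. Alpha 0.05, power 80%.

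**1. The plan's own figure.** Required number × (1 + 0.20):
- per group: 11 × 1.20 = 13.2, stated as 13;
- in total: 22 × 1.20 = 26.4, stated as 26.

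The stated figures are reproduced only by rounding down. The actual increase is (26 - 22)/22 = 18.2%. Rounded up, a full 20% increase is 14 per group, or 27 if only the total is rounded.

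**2. What 13 per group protects.** The largest loss that still leaves 11 is (13 - 11)/13 = 2/13 = 15.4%.

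| Loss | Left per group, 13 × (1 - loss) | Left in total, 26 × (1 - loss) |
|---|---|---|
| 10% | 11.7 | 23.4 |
| 15% | 11.05 | 22.1 |
| 20% | 10.4 | 20.8 |

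**3. If 20% is meant as the dropout allowed for.** Required number / (1 - 0.20):
- per group: 11/0.80 = 13.75, so 14, which leaves 14 × 0.80 = 11.2;
- in total: 28, against the stated 26.

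**4. What the shortfall does to power.** This depends on a test that the article does not name for the calculation. The standardised difference is d = 1.44/1.38 = 1.04.

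- *Two-sided two-sample t-test*, noncentrality d × √(n/2), with 2n - 2 degrees of freedom: 64% at 11 per group and 60% at 10.
- *Repeated-measures ANOVA, between-group effect*, with f = d/2 = 0.522, m = 3 measurements and a correlation of 0.5 (both my assumptions, as settings for the calculation), noncentrality N × f² × m/(1 + (m - 1) × 0.5): 81.3% at N = 22, 79.3% at N = 21 and 77.1% at N = 20.

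The second variant meets 80% at exactly 22, the plan's own number. Falling from 22 to 20 patients costs about 4 percentage points there (81.3 - 77.1 = 4.2). Under the t-test, falling from 11 to 10 per group costs about 5 (64.4 - 59.8 = 4.6).

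**The case against.** The best defence is that the article gives no 20% dropout rate. The 20% is the size of the increase, and 13.2 and 26.4 follow from it apart from a fraction of a patient. Read that way, the plan adds four patients and tolerates two losses per arm. Whether this is enough for ten sessions over two weeks and a 30-day visit cannot be judged from the document. The gap is also only one patient per arm, and it changes no endpoint or analysis.

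Much of this stands, and it rules out three stronger readings that a reader might infer.

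- *That the inflation is simply computed the wrong way, and the plan fails for the dropout it assumes.* This treats 20% as assumed attrition. It is the natural reading, since dropout is the only reason given for the increase, but it is not what the text states.
- *That power is 60% to 64%.* These figures hold only for a two-sided two-sample t-test, which the section does not name. They bear on the separate question of whether 11 per group follows from the pilot values.
- *That the chance of keeping enough patients is alarmingly low.* With independent 20% dropout, 13 per group gives a 25% chance of at least 11 in both arms. But 14 per group gives only 49%. Inflating to an expected value never guarantees a minimum, so this comparison says little about the choice of 13 over 14.

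The defence does not remove the rounding down, which is there on either reading. Nor does it supply the loss rate up to which the sample size is in fact secured.

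**Conclusion.** The point holds in a limited form and is minor. Two parts need no assumption about what 20% means: the increase was rounded down from 13.2 to 13 (18.2% in place of 20%), and 13 per group keeps the plan's minimum of 11 only up to about 15% loss. A third part is conditional: if 20% is the dropout allowed for, 14 per group (28) is the figure it implies, and 26 patients leave about 10.4 per group.

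The size is one patient per arm. That power falls below 80% at a 20% loss follows from the plan's own claim that 22 patients are required for 80%. By how much depends on the test: about 77% at N = 20 under the repeated-measures ANOVA with the assumptions above, or 60% at 10 per group under a two-sided t-test. Neither can be written into the protocol as an unconditional fact.

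**What to change.** Restate the dropout sentence in the Sample size section so that it says three things:

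- 13 per group (26) retains 11 per group for dropout up to about 15%;
- a 20% loss would leave about 10 per group, with power below the stated 80%;
- what dropout rate is assumed.

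If a power figure is added, give the test, the sidedness and, for repeated measures, the number of measurements and the correlation. If the 20% is to stand as the dropout allowed for, the target it implies is 14 per group (28).

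The cost of the restatement is one sentence and a slightly less favourable claim, with no extra patients. Keeping the 20% as a dropout allowance would cost two more patients.
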